**Methods:**

This is a multicenter, prospective, randomized controlled crossover trial with 2 parallel groups comparing PedAMINES with a conventional and internationally used drug infusion rate table in the preparation of continuous drug infusion. The evaluation setting uses a simulation-based pediatric CPR cardiac arrest scenario with a high-fidelity manikin. The study involving 120 certified nurses (sample size) will take place in the resuscitation rooms of 3 tertiary pediatric emergency departments and 3 smaller hospitals. After epinephrine-induced return of spontaneous circulation, nurses will be asked to prepare a continuous infusion of dopamine using either PedAMINES (intervention group) or the infusion table (control group) and then prepare a continuous infusion of norepinephrine by crossing the procedure. The primary outcome is the medication dosage error rate. The secondary outcome is the time in seconds elapsed since the oral prescription by the physician to drug delivery by the nurse in each allocation group. TDD includes TDP. Stress level during the resuscitation scenario will be assessed for each participant by questionnaire and recorded by the heart rate monitor of a fitness watch. The study is formatted according to the Consolidated Standards of Reporting Trials Statement for Randomized Controlled Trials of Electronic and Mobile Health Applications and Online TeleHealth (CONSORT-EHEALTH) and the Reporting Guidelines for Health Care Simulation Research.

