On the day of participation, nurses will complete a survey collecting data regarding their demographics, nursing training, and simulation and computer experience. After random allocation, each participating nurse will receive a standardized 5-minute training session on how to use the PedAMINES app. Nurses will remain unaware of specific endpoints of the study during this learning session. The simulation manikin characteristics are then presented. The nurses will then be asked to perform the pediatric resuscitation scenario, including post-ROSC. This scenario is standardized to follow the same chronological progression and range of difficulty to ensure each participant is exposed to exactly the same case, with similar challenges in decision making and treatment preparation provided on the same manikin. The uniform delivery of the scenario all along the study will minimize confounders. Study team members will only adapt to progression speed of participants through the scenario by maintaining a stressful resuscitation atmosphere. The scenario will be videorecorded and conducted in situ in the pediatric resuscitation rooms of each collaborating center to increase realism. High levels of realism are known to immerse participants in the simulated experience and prevent confounding variables that might potentially affect the way individuals perform [19]. On the day of participation, the resuscitation room will be exclusively devoted to the simulation to prevent unexpected interruption or external stimuli. Monitoring alarms will be activated to increase realism. All resuscitation equipment in the resuscitation room will be at the disposal of the nurse. In both allocation groups, the decision to use or not use any equipment will remain personal as in real life. Neither pilot testing nor repetitions will be permitted. There will be neither interventions nor educational adjuncts prior to or after the study period. Once the experiment is completed, the nurse will be required to recall and describe precisely how she prepared dopamine and norepinephrine in order to verify that the drug names and original doses prescribed by the physician were correctly understood to assess the presence of comprehension bias. Then, a quick oral debriefing, shorter than 5 minutes, on how the drugs were actually prepared and how they should have been prepared without errors will be provided to each participant by one of the study team members. The debriefing will focus on both preparation methods.

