
### Outcome Measures

The primary outcome of the study is the medication dosage error rate in each allocation group during the sequence from drug preparation to drug injection. A secondary outcome is the elapsed time in seconds, in each allocation group, between the oral prescription by the physician and drug delivery by the nurse. TDP completion by the nurse is included in TDD. Comparisons of medication errors and TDD between allocation groups in each hospital and between each of the 6 hospitals will be assessed as secondary outcomes. At the end of the scenario, a 4-item questionnaire using a 10-point Likert scale will be provided to the participants. The questionnaire measures (1) the overall stress perceived (On a scale of 1 to 10, how much stress did you feel during the whole resuscitation scenario?), (2) the stress perceived with PedAMINES (On a scale of 1 to 10, how much stress did you feel using PedAMINES?), (3) the stress perceived with the infusion rate table (On a scale of 1 to 10, how much stress did you feel using the infusion rate table?), and (4) the satisfaction about the preparation method used during the resuscitation scenario (On a scale of 1 to 10, how much satisfaction did you get during the resuscitation scenario with the help of PedAMINES and with the help of the infusion rate table?). A baseline heart rate (HR) before the beginning of the scenario as well as continuous HR monitoring of each participant reflecting his or her stress level will be recorded during the resuscitation scenario. Mean delta HR values (difference between HR peak values and baseline HR) will be obtained during some small segments of scenario and correlated to the scenario phases and the preparation methods used. The segments of interest are (1) when prompted to start the resuscitation because of asystole just before massage and ventilation, (2) when prompted to prepare dopamine either with PedAMINES or the infusion rate table, (3) the first 30 seconds when dopamine is being prepared, (4) the last 30 seconds when dopamine is being prepared, (5) the setting up of the pump, (6) the washout period, (7) when prompted to prepare norepinephrine either with PedAMINES or the infusion rate table, (8) the first 30 seconds when norepinephrine is being prepared, (9) the last 30 seconds when norepinephrine is being prepared, (10) at announcement of successful resuscitation achievement, and (11) 1 minute later. Acceptability and usability testing of the app will be assessed using a 52-item questionnaire based on the unified theory of acceptance and use of technology (UTAUT) model [20]. UTAUT provides a useful tool to assess the likelihood of success for new technology introductions and helps to understand the drivers of its acceptance.

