### Statistical Analysis

#### Primary Outcome

The rate of medication errors is the proportion of nurses committing a medication error. The rate of medication errors will be reported with 95% CI (Clopper-Pearson method) with each method and by study period to investigate a potential carryover effect. The error rates for each method will be compared using McNemar test for paired data. Differences in error rates will be reported with 95% CIs. Potentially, the efficacy of PedAMINES can be different according to the first method used in the crossover design (PedAMINES first: group A or the conventional preparation method first: group B). To investigate this potential effect, the difference in error rates (PedAMINES vs conventional method) will also be reported by randomized group (paired observations) and by period (independent observations). McNemar, chi-square, or Fisher exact test will be used to compare interventions. Errors will also be measured as the deviation in percent from the amount of delivered drug compared with the original dose prescribed by the physician. Absolute deviation will be analyzed. The mean (SD) difference in deviation obtained with each method will be reported with 95% CI. A *t* test for paired data will be used to compare interventions. Mean differences will be also reported by randomized group and by crossover period. We will assess the model for the presence of carryover and period effects following the Hills-Armitage approach to crossover study analysis [22]. The analysis of the primary outcome will be conducted for the university hospitals and for smaller hospitals.

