#### Secondary Outcomes

For TDD and TDP, the mean times will be reported with 95% CI for each arm and each study period to investigate a potential carryover effect. In case of a carryover effect, intervention arms will be compared within each study period using *t* tests for independent groups. If no carryover effect is found, data will be paired and analyzed using *t* tests for paired data.

For the primary and secondary outcomes, logistic regression analyses will be conducted to test a difference in rates of errors between university hospitals and smaller hospitals with PedAMINES and with the conventional preparation method. In a generalized estimating equation logistic regression model, an interaction between interventions and university/smaller hospitals will be tested to investigate a potential modification of the efficacy of PedAMINES in smaller hospitals compared with university hospitals. Analyses of primary and secondary outcomes will be conducted in nurses with more than 10 years of experience and in nurses with less than 10 years of experience. Means and standard deviations will be determined for stress and satisfaction scores of individuals for each questionnaire item as well as for the UTAUT questionnaire and reported with descriptive statistics. Pearson correlations will be computed between the HR measures obtained with the watch and the scenario phases for each of the preparation methods used. Data analysis will be carried out using GraphPad Prism version 6.0 (GraphPad Software, Inc) for graph figures, Stata/IC version 14 (StataCorp LLC) for descriptive analyses, and R version 2.15.2 (R Foundation) for statistical tests and 95% CI. Due to the nature of the interventions, we expect to have no missing data. In case of missing data, a complete case analysis will be conducted and no multiple imputation is planned. In order to assess interrater reliability on video reviewing, a kappa score—which provides a measure of interrater agreement independent of chance—will be calculated.

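### Drug and period are the same factor, so the planned carryover test cannot separate carryover from a difference in the app's benefit between dopamine and norepinephrine

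*Protocol article*

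**What the plan says.** The Abstract (Methods) fixes the drug order. The first task is dopamine: "nurses will be asked to prepare a continuous infusion of dopamine using either PedAMINES (intervention group) or the infusion table (control group"). The second drug follows with the other method, as the same sentence shows: "and then prepare a continuous infusion of norepinephrine by crossing the procedure". Outcome Measures confirms it through the heart-rate segments: "when prompted to prepare dopamine either with PedAMINES or the infusion rate table" comes before the washout and "when prompted to prepare norepinephrine either with PedAMINES or the infusion rate table" after it. Under Intervention, all nurses meet one scenario: "This scenario is standardized to follow the same chronological progression and range of difficulty to ensure each participant is exposed to exactly the same case". Randomization decides only which method comes first: PedAMINES in group A, the infusion rate table in group B.

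The Statistical Analysis section names carryover in three places:

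- Primary Outcome: "We will assess the model for the presence of carryover and period effects following the Hills-Armitage approach to crossover study analysis".
- Primary Outcome, on reporting error rates: "with each method and by study period to investigate a potential carryover effect".
- Secondary Outcomes, on time to drug delivery (TDD) and time to drug preparation (TDP): "the mean times will be reported with 95% CI for each arm and each study period to investigate a potential carryover effect". Here the finding has a consequence. If carryover is found, the methods are compared within each period by independent-groups t tests; if not, by paired t tests.

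Nothing in the article says that period and drug coincide.

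**The concern.** A carryover test in a two-period crossover compares the two-period totals of the two groups. It is easiest to defend when both periods pose the same task, because one can then argue that the method effect should not change between periods unless something carries over. Here the task changes by design. A nonzero contrast may mean that using one method first altered later performance with the other, or only that the app helps more with one drug.

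The error can go either way. A drug-specific benefit can be reported as carryover, or a drug difference can offset a real learning effect so that carryover is declared absent. For TDD and TDP the same result decides whether the paired analysis is kept. The by-period tables share the ambiguity, since period 1 against period 2 is dopamine against norepinephrine.

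**Working it through.** **Inputs from the article (Sample Size).** Error 15% with the app and 45% without; 5% of nurses err only with the app and 35% only without it; two-sided alpha 0.05; power 90%; 10 nurses per group per centre. With three centres per hospital set this gives 30 per group in each set and 60 per group overall. The share erring with both methods is 15% − 5% = 45% − 35% = 10%.

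**The plan's own figure.** McNemar sample size, with discordant share 0.40 and difference 0.30:

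n = [1.960·√0.40 + 1.282·√(0.40 − 0.30²)]² / 0.30² = (1.240 + 0.714)² / 0.09 ≈ 42.4, rounded up to 43.

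This matches the article, so the inputs are read correctly. The sample size is not in dispute.

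**What the contrast estimates.** Let b_D and b_N be the app's benefit (table minus app) for dopamine and norepinephrine, and λ_A, λ_B the carryover into period 2.

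- Group A total: app on dopamine + table on norepinephrine + λ_A
- Group B total: table on dopamine + app on norepinephrine + λ_B
- A − B = (b_N − b_D) + (λ_A − λ_B)

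Only the sum of the two brackets can be estimated. A drug that is harder by the same amount with both methods cancels from this contrast; it appears in the period contrast instead, where it cannot be told from time or learning.

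**Size for errors.** The drug-specific rates below are assumptions. App error is 15% for both drugs, table error averages 45%, there is no carryover, and the test is a two-sided 5% t test on totals. Rates are from simulation, with the within-nurse correlation set so that 10% err with both methods.

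| Table error, dopamine / norepinephrine | 60 v 60 | 30 v 30 |
|---|---|---|
| 45% / 45% | 5% | 5% |
| 35% / 55% | 39% | 22% |
| 30% / 60% | 71% | 43% |

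Hand check at the planned margins:

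- Covariance = 0.10 − 0.15·0.45 = 0.0325.
- Variance of a total = 0.1275 + 0.2475 + 2·0.0325 = 0.44, so SD = 0.663.
- Standard error at 60 v 60 = 0.663·√(2/60) = 0.121.
- A 20-point difference gives 0.20/0.121 = 1.65 and rejection of about 38%. A 30-point difference gives 2.48 and about 70%.

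When one drug is 10 points harder with both methods (table 40%/50%, app 10%/20%), rejection stays at 5%.

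Fisher's exact test comparing nurses who err twice with those who never err gives lower rates at 60 v 60: about 13% at 35%/55% and 28% at 30%/60%.

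**Masking (60 v 60).** A real carryover that lowers later table error by 20 points is detected about 40% of the time if the drugs are alike, and 5% if a 20-point drug difference exactly offsets it.

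**Size for TDD and TDP.** Assume a per-period SD of 1 and within-nurse correlation of 0.5. The SD of a total is √(1 + 1 + 2·0.5) = 1.732, and the standard error at 60 v 60 is 1.732·√(2/60) = 0.316. A time saving that differs between drugs by 0.5 SD gives 0.5/0.316 = 1.58 and about 35% false carryover findings (20% at 30 v 30).

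**The case against.** The strongest reply is that carryover is aliased with method-by-period interaction in every two-period, two-sequence crossover. That is so; the fixed drug order adds a concrete possible source of that interaction. The remaining points for the other side largely stand:

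- A reader might infer that the test is invalid. It is not: with equal benefit for both drugs it rejects at 5%.
- A reader might infer that unequal benefit is to be expected, since app errors in the pilot were 0/20 and a harder drug could then move only the table rate. The documents do not support this. They give no rate or time by drug, both drugs follow the same table procedure and the same app path, and the scenario appendix and the table figure are not shown.
- A reader might infer that the primary result is at risk. The McNemar comparison is planned unconditionally, and no action follows a positive carryover test on errors.
- The by-period differences between methods are already planned, so the by-drug estimates will exist.
- The sentence naming the Hills-Armitage approach follows the analysis of percentage deviation, and the article does not say that it means a t test on summed binary errors.
- If the apparent carryover is really a drug-specific benefit, the fallback for times gives valid estimates for each drug and loses only the efficiency of pairing.

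The alias itself survives all of this, as do its lack of mention and the rule that lets the test choose the TDD and TDP analysis.

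**Conclusion.** The concern holds in a limited form. The design cannot separate carryover from a method-by-drug difference, or a period effect from a drug effect, yet the article plans to draw conclusions on both. The algebra follows from the fixed drug order and needs no assumption about error rates. The frequencies do: no false excess if the drugs benefit equally, and about 39% to 71% false carryover findings with 60 per group (22% to 43% with 30) for assumed benefit gaps of 20 to 30 points under a t test on totals, with a Fisher version lower. The masking figure assumes exact cancellation. The practical consequence lies in the interpretation of the crossover checks and in the conditional analysis of TDD and TDP, not in the primary comparison. The change should be made, but the trial's main conclusion does not hang on it.

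**What to change.** In the Primary Outcome and Secondary Outcomes parts of Statistical Analysis:

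1. Describe the contrast as carryover and/or method-by-drug interaction, and draw no conclusion that carryover is present or absent. Describe a period effect as a period and/or drug effect.
2. Remove the rule that lets this test choose the TDD and TDP analysis. Keep the paired comparison as pre-specified and always report the within-period comparisons beside it.
3. Label the by-period differences already planned as the dopamine and norepinephrine results, with 95% CIs, and note that only the period 1 (dopamine) comparison between groups is free of carryover.

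The cost is wording and table labels, with no new data and no more nurses. The trial gives up the claim that carryover was tested and found or excluded. Changing the drug order partway through is not proposed, since it would depart from the single standardized scenario.

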#### Secondary Outcomes

For TDD and TDP, the mean times will be reported with 95% CI for each arm and each study period to investigate a potential carryover effect. In case of a carryover effect, intervention arms will be compared within each study period using *t* tests for independent groups. If no carryover effect is found, data will be paired and analyzed using *t* tests for paired data.

For the primary and secondary outcomes, logistic regression analyses will be conducted to test a difference in rates of errors between university hospitals and smaller hospitals with PedAMINES and with the conventional preparation method. In a generalized estimating equation logistic regression model, an interaction between interventions and university/smaller hospitals will be tested to investigate a potential modification of the efficacy of PedAMINES in smaller hospitals compared with university hospitals. Analyses of primary and secondary outcomes will be conducted in nurses with more than 10 years of experience and in nurses with less than 10 years of experience. Means and standard deviations will be determined for stress and satisfaction scores of individuals for each questionnaire item as well as for the UTAUT questionnaire and reported with descriptive statistics. Pearson correlations will be computed between the HR measures obtained with the watch and the scenario phases for each of the preparation methods used. Data analysis will be carried out using GraphPad Prism version 6.0 (GraphPad Software, Inc) for graph figures, Stata/IC version 14 (StataCorp LLC) for descriptive analyses, and R version 2.15.2 (R Foundation) for statistical tests and 95% CI. Due to the nature of the interventions, we expect to have no missing data. In case of missing data, a complete case analysis will be conducted and no multiple imputation is planned. In order to assess interrater reliability on video reviewing, a kappa score—which provides a measure of interrater agreement independent of chance—will be calculated.

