### Sample Size

The primary objective of this study is to detect a difference in rates of medication errors between groups (with PedAMINES vs without PedAMINES). In our crossover pilot study conducted in a single university hospital, the rate of medication errors was 70% (14/20, 95% CI 46%-88%) without PedAMINES and 0% (0/20, 95% CI 0%-17%) with PedAMINES [14]. We aim to reproduce these results in 3 university hospitals and 3 smaller hospitals. The sample size was calculated to have a power of 90% to detect a difference of at least 30% in rates of medication error between intervention groups in both sets of hospitals (university and smaller hospitals). We consider that a difference of 30% in the rate of medication errors is sufficient to modify the practice. We assumed a rate of error of 15% with PedAMINES and 45% without PedAMINES. Since this study is a crossover, observations will be paired and a McNemar test will be used to compare the rate of errors between intervention groups. For the sample size calculation, we assumed that 5% of nurses will commit a medication error with PedAMINES but not without PedAMINES and that 35% of nurses will commit a medication error without PedAMINES but not with PedAMINES (Multimedia Appendix 2). With a 2-sided risk alpha of 0.05, the needed sample size is 43 nurses for each set of hospitals. Finally, 8 nurses per randomized group must be recruited in each participating center (16 nurses per center). To prevent a potential loss of power due to misspecification of assumptions, 10 nurses will be recruited per randomized group and per participating center (total sample size: 120 nurses).

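### A carryover check on the same data chooses the TDD and TDP test, so the nominal 5% level is not held, and the check cannot tell carryover from a drug difference

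*Protocol article*

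**What the plan says.** For TDD and TDP, the Secondary Outcomes section states that "the mean times will be reported with 95% CI for each arm and each study period to investigate a potential carryover effect". Two branches follow. The first begins "In case of a carryover effect, intervention arms will be compared within each study period using", and the test it names is the two-sample t test. The second begins "If no carryover effect is found, data will be paired and analyzed using", and there the test is the paired one. The section names neither the carryover statistic nor its significance level. When carryover is found it keeps both periods and does not say which one decides.

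A named method appears only under Primary Outcome: "We will assess the model for the presence of carryover and period effects following the Hills-Armitage approach to crossover study analysis". The Abstract (Methods) fixes the order of tasks. Every nurse prepares dopamine first with one method "and then prepare a continuous infusion of norepinephrine by crossing the procedure". The scenario segments listed under Outcome Measures follow the same order.

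**The concern.** A rule that tests for carryover and then selects the treatment comparison from the same data has three weaknesses here.

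- The carryover statistic is correlated with the within-period contrasts to which the rule switches. The second test therefore does not run at its nominal level once the first is positive.
- If carryover is real, the period-2 contrast mixes it with the method effect, yet period 2 belongs to the fallback.
- Drug and period coincide, so an app that saves more time on one drug than on the other looks like carryover and sends the analysis to the less precise between-nurse tests.

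TDP and TDD are named in the trial's Objective, so the error rate and precision of these comparisons matter even though they are secondary.

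**Working it through.** **The plan's own figure.** The only sample-size figure concerns the primary outcome: "With a 2-sided risk alpha of 0.05, the needed sample size is 43 nurses for each set of hospitals". With discordant rates 0.35 and 0.05, n = [1.960·√0.40 + 1.282·√(0.40 − 0.30²)]² / 0.30² = 42.4, rounded up to 43. It reproduces, and nothing below depends on it. The plan states no error rate or power for TDD or TDP.

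**Inputs from the Sample Size section.** Ten nurses per randomized group per centre give 6 × 10 = 60 per sequence overall and 3 × 10 = 30 per sequence in each hospital set. The two-sided 0.05 level is stated for the primary outcome and assumed here for the times.

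**Assumptions not in the document.** Normal data with unit SD; within-nurse correlation ρ from 0 to 0.75; carryover checked by a two-sample t test on each nurse's two-period sum (the usual reading of Hills-Armitage) at 0.05.

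**1. The stages are linked.** The correlation between the sum contrast and the period-1 contrast is √((1+ρ)/2): 0.71 at ρ = 0, 0.87 at 0.5 and 0.94 at 0.75.

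**2. Error rate of the rule as written.** Simulation with no method effect and no carryover, ρ = 0.5, 60 per sequence, 40,000 trials per row:

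| Period (drug) effect | Paired t alone | Rule, period 1 decides | Rule, either period counts | Period-adjusted test alone |
|---|---|---|---|---|
| 0 | 4.9% | 7.3% | 9.1% | 4.9% |
| 0.5 SD | 2.8% | 5.3% | 7.0% | 5.0% |
| 1 SD | 0.6% | 3.3% | 5.0% | 4.9% |

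Across ρ = 0 to 0.75 and 30 or 60 per sequence, the two rule columns are about 6%-8% and 8%-10% with no period effect, about 5% and 6%-7% at 0.5 SD, and about 3% and 5% at 1 SD.

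The fall is explained by the paired test. At ρ = 0.5 the within-nurse difference has variance 2(1 − ρ) = 1. Pooling the sequences without a period term adds the squared period effect, giving 1.25 at 0.5 SD and 2 at 1 SD. The effective critical values become 1.96·√1.25 = 2.19 and 1.96·√2 = 2.77, with two-sided tails of 2.8% and 0.6%, as in the table.

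**3. After a positive check.** With no effect of any kind, the period-1 test rejects about 30%-67% of the time, rising with ρ (52% at ρ = 0.5).

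**4. Period 2 under real carryover.** Let τ be the method effect (app minus table) and λ the carryover in the app-first sequence relative to the other. The period-2 contrast estimates τ − λ. At ρ = 0.5 and 60 per sequence:
- τ = 0, λ = 0.5 SD: the check fires in only 35% of trials; when it does, the period-2 test rejects 99.6% of the time.
- τ = λ = −0.5 SD: when the check fires, the period-2 test rejects only 6.7% of the time, so a real effect is hidden.

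**5. What the check measures.** Write P for the app and T for the table. The sequence-sum contrast is (P_dop + T_nor) − (T_dop + P_nor) = (P − T)_dop − (P − T)_nor, which is the method-by-drug interaction. For an assumed interaction of 0.5 SD, the noncentrality is 0.5 / (2·√((1+ρ)/n)) = 0.25·√(n/(1+ρ)):

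| n per sequence | ρ = 0 | ρ = 0.5 | ρ = 0.75 |
|---|---|---|---|
| 30 | 1.37 (27%) | 1.12 (20%) | 1.04 (17%) |
| 60 | 1.94 (48%) | 1.58 (35%) | 1.46 (31%) |

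Percentages are the chance of switching analysis, against 5% with no interaction.

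**The case against.** The strongest reply is that a reader might infer that the rule always pushes the false-positive rate above 5%. The document does not support that. The no-carryover branch is an unadjusted paired t test, and a difference between the two drugs, plausible in this design, makes it conservative. At a period effect of 1 SD the rule as written is at or below 5%. This part of the objection stands. It does not rescue the rule: the offset comes from a second weakness that costs power. If the second stage were period-adjusted, the inflation would remain (7.4% or 9.1% at 1 SD, ρ = 0.5).

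Other fair points:
- The sum test and its level are inferred. Hills-Armitage is named only under Primary Outcome, and the detail may sit in a document not shown.
- The either-period figures need a decision rule that the text does not state. If both periods had to be significant, the rate would be 4.7%-6.8% with no period effect.
- A reader might take the fallback to be period 2 alone. It covers both periods, and carryover cannot bias period 1.
- The 30%-67% is conditional on a check that fires in about 5% of null trials.
- Means with intervals by arm and period are reported whichever branch is taken, so period-1 results stay visible.
- The average power loss from switching can be small: for a 0.5 SD effect, 30 per sequence and ρ = 0.5, power is 94.4% under the rule (period 1) against 96.8% if always paired.

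These points limit the size and severity of the concern. They do not remove the data-driven choice of test, or the fact that its trigger cannot be interpreted as carryover.

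**Conclusion.** The concern holds in a limited form. The rule does not hold its nominal 5% level for TDD and TDP. Depending on the period effect and on which period decides, the rate runs from about 3% to about 10%, so it can be anti-conservative or conservative. These figures rest on the assumed sum test at 0.05, correlation 0 to 0.75, normal data and period effects of 0 to 1 SD.

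Two parts do not depend on those rates. Real carryover biases the period-2 comparison, and the trigger cannot separate carryover from a method-by-drug interaction because drug and period coincide. The trigger frequencies do depend on the assumed 0.5 SD interaction.

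A reader might extend the point to the primary outcome. The text does not support that: the overall McNemar comparison is not switched on a carryover result. With only secondary outcomes affected, this should be fixed but does not threaten the main conclusion.

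**What to change.** Delete the conditional rule for TDD and TDP and state instead:

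1. The analysis is always the period-adjusted within-nurse estimate: a two-sample t test between sequences on each nurse's period-1 minus period-2 difference, with the difference in means halved. It estimates the method effect averaged over the two drugs and held 4.8%-5.1% type I error for period effects of 0 to 1 SD.
2. The period-1-only comparison is a fixed sensitivity analysis, reported whatever the carryover result. It is needed because the within-nurse estimate is itself shifted by −λ/2 if carryover is real.
3. The sequence contrast is reported with its confidence interval as descriptive, labelled *carryover or method-by-drug, not separable*, and does not choose the test.

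The cost is a few sentences in the statistical section. No new data or extra nurses are needed. The change should be made before the times are analysed.
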